### Sample size calculation

No previous data is available on live birth following individualized lifestyle intervention in PCOS women who wish to conceive. From previous study performed in one of the trial sites, the live birth rate following usual care which consisted of one-time lifestyle advise and ovulation induction with Letrozole for up to five treatment cycles, was reported as 30% [25]. Due to uncertainty about the likely event rate (live birth rate) in the intervention arm, it was assumed that to convince the clinicians and patients to adopt a change in practice, a modest improvement of 10% in live birth would be required.

For alpha error set at 0.05 and power being 90%, to detect a clinically relevant difference of 10% in the live birth rate following individualized lifestyle intervention, the calculated sample size will be 473 in each arm (total sample size 946). Assuming an attrition of 20%, the total sample size was 1183. We rounded off the total sample size to 1200 with 600 in each arm. With 5 centres participating in the study each site shall recruit 240 subjects each.

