### Statical analysis

Data will be entered using ICMR software (developed by ICMR, New Delhi) and screened for outliers and extreme values using Box-Cox plot and histogram (for the shape of the distribution). Summary statistics will be used for reporting demographic and clinical characteristics using mean (SD)/median (range) for the continuous variables, and frequency along with percentage for categorical variables. An intention-to-treat analysis and per-protocol analysis for the primary and secondary endpoints will be performed. The continuous endpoints will be tested using *z*-test for means, and the difference in means will be presented with 95% CI. The categorical endpoints will be tested using *z*-test for proportions and the difference in proportion will be presented with 95% CI. A generalized estimating equations (GEE) will be performed to understand the compliance and the effect over time between the two groups of intervention. To understand the advantage of intervention the number needed to treat will be presented.

Based on BMI 23–27 and > 27–35 kg/m^2^, we will perform subgroup analysis to explore whether there is any difference in the effect of the intervention in different subpopulations.

All the randomized subjects will be included in the intention to-treat (ITT) analysis. The ITT analysis is done for the primary endpoint and secondary endpoints and analysed according to the group assigned by randomization. For dropouts with no information on the outcome, it will be assumed that the intervention did not result in a live birth (Table 1).

Per-protocol set (PPS) is the subset of ITT, where the subjects are randomized and treated without any major protocol deviations that impacts the efficacy of the results. The PSS will be used for primary endpoint analysis and secondary end-points. The analysis set will be the subset of participants who are not dropped out of the study and satisfy the protocol requirement. Non-compliant will not be considered for the per-protocol analysis but will be included in the ITT (Table 1). We will perform additional analysis for partially compliant participants and include them in the per-protocol analysis (Table 1). The analysis will be performed by creating an interaction term for the intervention group with partially and fully complaint groups presenting multiple testing-adjusted *p*-values.

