## Discussion

Lifestyle intervention is considered as the first line of management for treating PCOS women who present with infertility. While earlier studies have shown some improvement in menstrual symptoms, endocrinological parameters and ovulation rate, very few have reported clinically important fertility outcomes, i.e. live birth [11–14]. The current trial is planned to capture all the relevant clinical domains which are important to the PCOS women such as reproductive outcomes, improvement in menstrual symptoms, changes in anthropometric measurements and endocrinological parameters and, finally, the quality-of-life score.

High dropout rates and adherence issues are some of the challenges in trials evaluating lifestyle intervention [10, 26]. The Cochrane review evaluating the lifestyle intervention reported high dropout rates (up to 46%), especially in studies involving longer treatment periods [10]. A systematic review investigated the dropout rates in studies evaluating the lifestyle intervention in overweight and obese infertile women [26]. The review included 15 studies, out of which 10 reported the dropout rate. The median dropout rate was 24% (range 0–31%). The authors could not find any modifiable predictors for dropouts and reported lower weight loss in women who had dropped out of the trial. The current study has calculated the sample size taking into account the possibility of high attrition (20%) that may be encountered during the conduct of the trial. In the currently planned trial, it has been hypothesized that customized lifestyle intervention delivered by the medical staff other than the treating clinician may help in greater adherence and lower dropouts. The study will indirectly help us investigate the impact of such an approach on the attrition rate for the lifestyle intervention.

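### The 20% inflation assumes that dropouts leave the analysis, but the ITT rule keeps them as no live birth: power is then about 87%, not 90%, and unequal dropout would bias the comparison

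*Protocol article*

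**What the plan says.** Protocol article, Sample size calculation. The control live-birth rate comes from an earlier study at one of the sites, where the rate after usual care with "ovulation induction with Letrozole for up to five treatment cycles, was reported as 30" per cent. The target is stated as "a modest improvement of 10% in live birth would be required", and the error rates as "For alpha error set at 0.05 and power being 90" per cent. This gives 473 per arm, 946 in total. Then: "Assuming an attrition of 20%, the total sample size was 1183", rounded to 1200, or 600 per arm.

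Protocol article, Statical analysis. All randomised women enter the ITT analysis in their assigned arm, proportions are compared by a z-test, and "For dropouts with no information on the outcome, it will be assumed that the intervention did not result in a live birth".

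Follow-up contact differs by arm. The intervention arm gets weekly messages, monthly calls and a week 13 visit (the subsections for weeks 2 to 12, week 13 and weeks 14 to 25). The Control section plans no compliance follow-up and a review at 6 months. Both arms may have up to three letrozole cycles from month 3.

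On attrition, the Discussion cites a review of lifestyle studies with median dropout of 24% and a range up to 31%. It suggests that delivery by staff other than the treating clinician "may help in greater adherence and lower dropouts".

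**The concern.** The sample size section and the analysis section treat the same women in two ways. Dividing by 0.8 replaces women who will be missing from the analysis, so that 473 per arm remain with rates of 30% and 40%. The ITT rule removes nobody. It scores women with unknown outcomes as failures, which shrinks both rates and the difference between them. The extra women recruited do not fully make up for the smaller difference.

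The second problem is direction. Under this rule a woman's recorded result depends on whether she can be found. Dropout is defined by the 3- and 6-month visits, while live birth is counted up to 16 months, so a dropout may well have a live birth that nobody records. If one arm is followed more closely, it will show more live births for that reason alone. The stakes are a power statement that does not describe the planned test, and a primary comparison exposed to differences in retention.

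**Working it through.** **Reproducing the plan.** Inputs from Sample size calculation: 30% against 40%, alpha 0.05, power 90%. Sidedness is not stated; two-sided reproduces the figure.

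n = (1.96 + 1.2816)² × (0.3×0.7 + 0.4×0.6) / 0.10² = 472.8, so 473 per arm. 946 / 0.8 = 1182.5, so 1183. Both agree with the plan. With 20% excluded from 600, 480 per arm at 30% against 40% gives 90% power, as intended.

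**Power under the ITT rule, equal dropout.** Let d be the share with unknown outcome in each arm, and take 30% and 40% as rates among women with known outcomes. The tested rates are 0.30(1−d) and 0.40(1−d), with n still 600 per arm. SE = √[(pC(1−pC) + pI(1−pI))/600], and power = Φ(difference/SE − 1.96).

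| d | Tested rates | Difference | SE | Power |
|---|---|---|---|---|
| 14% | 25.8% vs 34.4% | 0.086 | 0.02637 | 90% |
| 15% | 25.5% vs 34.0% | 0.085 | 0.02628 | just under 90% |
| 20% | 24.0% vs 32.0% | 0.080 | 0.02582 | 87% |
| 24% | 22.8% vs 30.4% | 0.076 | 0.02542 | 85% |
| 31% | 20.7% vs 27.6% | 0.069 | 0.02463 | 80% |

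Pooled variance gives the same rounded figures at 20%, 24% and 31% (87.1%, 84.7%, 79.8%). If 30% and 40% already count unknown outcomes as failures, no shrinkage applies and 600 per arm gives 95%.

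**No treatment effect, unequal dropout.** The protocol gives no dropout by arm, so these inputs are assumptions: 30% overall live-birth rate in both arms, dropout 20% in control and 10% in intervention, and live-birth rate r among dropouts. Recorded rate = 0.30 − d×r, so the false difference is (0.20 − 0.10)×r.

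| r | Recorded rates | False difference | Rejection, two-sided |
|---|---|---|---|
| 10% | 28% vs 29% | 1 point | 7% |
| 20% | 26% vs 28% | 2 points | 12% |
| 30% | 24% vs 27% | 3 points | 22% |

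With equal dropout and no effect, the recorded rates are equal and the test holds 5%.

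**How the two relate.** With a true 30% against 40% and the same 20%/10% split (r equal to the arm's own rate), the tested rates are 24% and 36% and power is 99.6%, not reduced. If the intervention arm loses more women (15% control, 25% intervention), the tested rates are 25.5% and 30%, and power falls to 41%.

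**Control rate over three cycles.** Assuming a constant per-cycle rate and full use of all cycles: 1 − 0.7^(1/5) = 0.0689 per cycle, and 1 − 0.7^(3/5) = 0.193 over three. A 10-point gain with 20% scored as failure, by the formula above:

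| Control rate | Tested rates | Power | Ratio |
|---|---|---|---|
| 19.3% | 15.4% vs 23.4% | 94% | 29.3/19.3 = 1.52 |
| 25% | 20% vs 28% | 90% | 35/25 = 1.40 |
| 30% | 24% vs 32% | 87% | 40/30 = 1.33 |

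**The case against.** The other side has several good points.

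- **The sample size arithmetic is right.** Both 473 and 1183 reproduce. The fault is that the inflation does not match the analysis rule.
- **A reader might infer that the trial simply lacks 90% power.** The documents do not support that. The loss requires that 30% and 40% are rates among women with known outcomes, and that all of the 20% attrition has no outcome information. The rule covers only dropouts whose outcome is unknown. The protocol says neither how the source study counted its losses nor how many dropouts will be untraceable.
- **A reader might infer that the primary test has a 22% false-positive rate.** That figure is the top of a range built on an assumed split and on dropouts having live births as often as other women. Dropouts may miss the letrozole cycles, so a lower rate among them is quite possible. With equal dropout there is no inflation.
- **A reader might take the Discussion as forecasting lower dropout in the intervention arm than in control.** It credits delivery by staff other than the treating clinician, and control women also see the dietician and physiotherapist once. What supports possible imbalance is the contact schedule. Even there, control women have fertility-treatment contact from month 3, and a more demanding programme could instead raise dropout.
- **A reader might infer that three cycles rather than five leave the trial underpowered.** The plan targets an absolute 10-point difference, not a ratio, and at a lower control rate that difference has more power. The 19% also ignores conceptions before letrozole starts, which count here.

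What stands is the mismatch between inflation and rule, and the dependence of the primary comparison on retention. Both the sample size and the rule are fixed in this document, so neither is merely left to an analysis plan.

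**Conclusion.** The point holds in conditional form. If 30% and 40% are rates among women with known outcomes and 20% per arm are unknown, the planned test has about 87% power rather than 90%: a modest gap, growing to 85% and 80% at the 24% and 31% dropout that the Discussion cites. There is no shortfall up to about 14% unknown, or if the two rates already count losses as failures.

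The possible bias is the weightier part, though its size cannot be fixed from the documents. It needs both unequal dropout and live births among dropouts. The unequal contact schedule makes the first plausible, and under the assumed 20%/10% split the effect ranges from slight to serious. The power loss arises under equal dropout. Retention that favours the intervention arm raises rejection instead, so the two should not be summed.

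The difference in cycle number is a matter of disclosure: the control rate may be below 30%, and a 10-point gain would then be a larger relative gain than the sample size section implies.

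**What to change.** 1. Restate power under the ITT rule: about 87% at 20% and 85% at 24% unknown outcomes. Say whether 30% and 40% are rates among women with known outcomes or per woman randomised. Recruiting back to 90% at 20% unknown would take 660 per arm (pooled variance), so reducing unknown outcomes is the cheaper route.
2. Seek live-birth status by phone or records, in the same way in both arms, for every randomised woman who has not withdrawn consent, including those who miss visits. A mobile phone in the house is already an entry condition. This reduces both problems at their source.
3. Beside the analysis that scores dropouts as no live birth, prespecify a sensitivity analysis, unless the full analysis plan already has one: multiple imputation by arm using site, BMI stratum and baseline data, with a range of assumptions about live births among dropouts. Imputation alone assumes outcomes missing at random, which is doubtful if dropouts also miss treatment, hence the range. Whether imputation should be primary is a matter on which statisticians differ, and this point does not require it.
4. State that the 30% comes from up to five cycles while this trial gives up to three, and give the relative gain that a 10-point difference would mean at a lower control rate (about 1.52 at 19%).

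The cost is a slightly less favourable power figure, some phone calls and one extra analysis. The changes should be made before outcomes by arm are seen.

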**Control arm**		
At 6 months	Point of assessment 3	Point of assessment 4
Ovulation induction with letrozole	Yes	Yes

For per protocol analysis inclusion only

• Compliance: for a minimum of three points of assessment and at least one ovulation induction cycle with letrozole (intervention arm)

• Compliance: for both the time points (3 and 4) and at least one ovulation induction cycle with letrozole (for control)

Additional analysis (partial compliance)

• Compliance for at least 2 time points of assessment in the intervention (per protocol will include full compliance and those who were partially compliant) and at least one cycle of ovulation induction

• Compliance at least in 1 time point plus at least one cycle of ovulation induction in the control arm

The following will be included in the intention-to-treat analysis only (not included in per protocol or additional analysis)

• Compliance for less than 2 time points irrespective of ovulation induction for intervention

• Compliance for no time points irrespective of ovulation induction for control

• Did not take ovulation induction irrespective of compliance for both the arms

• Who were dropouts (did not turn up at 6 months)

• Did not receive intervention for at least 4 months

Criteria for deciding non-compliance at each visit:

• Diet: participant consuming > 100 cal over the recommended calories intake

• Exercise: participant GPAQ score < 600

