#### Between weeks 2 and 12 (up to the end of the 3rd month) (only for the intervention arm)

Once a week text messages and/or videos on diet and physical exercise to re-in force the intervention.

Once a month telephonic contact to assess compliance with diet/exercise with the participant.

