#### Week 13– (session 2) (only for the intervention arm)

In person to check compliance for diet and physical exercise, check weight and anthropometric parameters and as the pregnancy status of the participants. An ultrasound will be performed before initiating ovulation induction.

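### The planned arm-by-compliance interaction crosses treatment with post-randomisation classes that are built differently in each arm, so it mixes selection with any effect of compliance

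*Protocol article*

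**What the plan says.** The section headed Statical analysis in the protocol article plans an extra analysis of partially compliant women. It is to be done by "creating an interaction term for the intervention group with partially and fully complaint groups", with p-values adjusted for multiple testing.

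Table 1 defines the classes:

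- **Intervention arm.** There are four checks, diet and exercise at month 3 and again at month 6. Full compliance is at least three. The partial level is "Compliance for at least 2 time points of assessment in the intervention" arm.
- **Control arm.** There are two checks, diet and exercise at month 6 only. Full compliance is both. The partial level is "Compliance at least in 1 time point plus at least one cycle of ovulation induction in the control arm".
- **Both arms.** At least one letrozole cycle is required. Women without one stay in the intention-to-treat analysis only.

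The schedule gives the intervention arm alone weekly messages, a month-3 visit and "Once a month telephonic contact to assess compliance with diet/exercise with the participant". Letrozole starts after month 3 in women who have not conceived. The same statistical section plans intention-to-treat and per-protocol analyses and a GEE model of compliance and effect over time.

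**The concern.** An interaction between arm and a subgroup can be read causally when the subgroup is fixed at baseline and means the same in both arms. Neither holds here.

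1. The class is observed after randomisation, and the programme is designed to change it. A woman who complies with regular reminders is, on average, less selected than one who complies after a single session.
2. The label is a different variable in each arm: three of four checks over two visits against two of two at one visit.
3. The letrozole condition removes women who conceive early, so class membership depends partly on the outcome pathway.

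The contrast within each class is therefore not randomised, and neither is the difference between the two contrasts. Adjusting p-values controls chance findings across several tests; it leaves this bias in place. At stake is how readers interpret benefit by compliance, in a trial whose Discussion treats adherence as a central challenge. Better-working reminders can widen the distortion.

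**Working it through.** **Yardstick.** The plan gives no figure for this analysis. Its sample size shows which differences matter: 30% v 40%, two-sided alpha 0.05 (the sidedness is assumed; two-sided reproduces the figure), power 90%. This gives (1.960 + 1.282)² × (0.3×0.7 + 0.4×0.6) / 0.10² = 472.8, so 473 per arm as stated. 946 / 0.8 = 1182.5, so 1183 as stated. The target difference is 10 points.

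**Step 1: the classes differ even with identical behaviour.** Let every check be passed independently with probability p. For the intervention arm, full = P(Bin(4,p) ≥ 3) and partial = P(Bin(4,p) = 2). For controls, full = p² and partial = 2p(1−p). Partial here means partial but not full.

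| p | Full, intervention v control | Partial, intervention v control |
|---|---|---|
| 0.60 | 47.5% v 36.0% | 34.6% v 48.0% |
| 0.70 | 65.2% v 49.0% | 26.5% v 42.0% |

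**Step 2: no true effect, reminders raise compliance.** The documents give no compliance rates and no link between adherence and live birth, so these inputs are assumptions. Half the women are more adherent by nature (live birth 40%) and half less (24%), whichever arm they are in. Live birth in a class is 24% + 16% × (share of more adherent women in it). The letrozole condition is left out of this step.

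*Scenario A:* per-check pass rates 90%/60% (intervention) v 70%/20% (control).
- Full: the share of more adherent women is 0.9477/(0.9477+0.4752) = 66.6% v 0.49/(0.49+0.04) = 92.5%. Live birth is 34.7% v 38.8%, a difference of **-4.1**.
- Partial: the share is 0.0486/(0.0486+0.3456) = 12.3% v 0.42/(0.42+0.32) = 56.8%. Live birth is 26.0% v 33.1%, a difference of **-7.1**.
- Interaction: -4.1 − (-7.1) = **+3.0** points.

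*Scenario B:* 80%/50% v 60%/30%.
- Full: the share is 72.4% v 80.0%. Live birth is 35.6% v 36.8%, **-1.2**.
- Partial: the share is 29.1% v 53.3%. Live birth is 28.6% v 32.5%, **-3.9**.
- Interaction: **+2.7** points.

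**Step 3: when this bias disappears.**
- If live birth is the same in both adherence groups, every difference is 0.
- If reminders change nothing, the full/partial differences are +0.6/+1.0 at 70%/20% in both arms, and +0.8/+0.5 at 60%/30%.

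**Step 4: a second model.** One continuous adherence trait drives both the checks and live birth. Assumptions: control live birth 30%, control per-check pass rate 40%, full compliance 24% in controls and 52–68% with the programme, and log-odds of live birth per SD of the trait of 0.3 to 0.8.
- With no true effect, the difference is -2.4 to -10.0 points in full compliers and -2.8 to -12.0 in partial compliers. The interaction odds ratio is 1.03 to 1.25 instead of 1.00.
- With a true benefit of +5 points, the full-complier difference runs from +3.0 to -4.3.

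**Step 5: the letrozole condition alone.** Assume 30% live birth in both arms, 80% of early conceptions ending in live birth, and early conception in 6% of controls v 10–12% of intervention women. Among the remaining women:
- Control: (0.30 − 0.048)/0.94 = 26.8%.
- Intervention: (0.30 − 0.080)/0.90 = 24.4%, or (0.30 − 0.096)/0.88 = 23.2%.
- The difference is -2.4 to -3.6 points, although the intention-to-treat difference is zero.

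**The case against.** The strongest reply is that this is an additional analysis. The intention-to-treat analysis keeps all randomised women, the Discussion already concedes that adherence is hard to assess, and every rate above is assumed. The sizes are also modest against sampling error. With 600 per arm and no losses, Scenario A has standard errors of about 4.5 points (full), 5.1 (partial) and 6.8 (interaction), so none of the biases reaches 1.5 standard errors. All of this stands, and it limits the consequence. It does not make the contrast interpretable, because the bias shifts the estimate whatever its precision.

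A reader might infer more than the documents support:

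- *That the interaction is the plan's only look at compliers.* It is not; per-protocol and GEE analyses are also planned.
- *That it shows selection instead of a dose effect.* It mixes selection with any real effect of compliance and cannot separate them. The protocol does not call it a dose effect.
- *That the interaction term itself would signal harm.* In both reminder scenarios the false harm lies in the within-class differences. The interaction is positive, making full compliers look better off than partial ones.
- *That the direction is fixed.* It depends on the assumptions. With equal compliance in both arms the small differences above are positive.

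**Conclusion.** The point holds in this form. The rule as written gives a non-randomised contrast between classes that are defined differently by arm, shifted by reminders in one arm and conditioned on letrozole use. Multiplicity adjustment does not address that.

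Under the two reminder scenarios with no true effect, the bias is about -1 to -4 points in full compliers, -4 to -7 in partial compliers and about +3 in the interaction, against a design difference of 10. The continuous-trait model gives larger values at its stronger settings. These figures are illustrations, because the protocol supplies neither compliance rates nor a link between adherence and prognosis. The adherence bias is zero if adherence is not prognostic and near zero if reminders leave compliance unchanged. The letrozole route is separate and needs the programme to alter early conception.

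It would be wrong to conclude that the primary result is compromised: the intention-to-treat analysis does not use these classes.

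**What to change.** **Minimum change.** Do not use the interaction for inference on benefit by compliance. Drop it, or report it as descriptive and non-causal.

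**If an effect in compliers is wanted.** Report a complier-average effect on all randomised women, with randomisation as the instrument: the intention-to-treat difference in live birth divided by the proportion of intervention women who reach the threshold, with a bootstrap or two-stage interval. It is zero when the intention-to-treat difference is zero. The plan should then:

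- Define compliance as engagement with the structured programme, which controls do not receive. The Table 1 calorie and GPAQ criteria will not serve, because controls get advice too and can meet them.
- Leave out the letrozole-cycle condition, and state a rule for women who conceive before a check.
- Fix one threshold in advance. The lower, at-least-partial level is the less demanding assumption.
- State the exclusion restriction: allocation has no effect in women below the threshold.
- Not present two thresholds as a dose-response or a sensitivity range, since both share one numerator. With Scenario A shares and an assumed intention-to-treat difference of +5, the full threshold gives 5/0.711 = 7.0 points and at-least-partial gives 5/0.909 = 5.5. That gap is arithmetic only.

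**Cost.** Revised analysis wording and a standard estimator in Stata. Existing contact and visit records should suffice if engagement is defined from them. The price is a wider interval and an assumption that cannot be tested.
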